## Abstract

**Background:**

Musicians are at high risk for playing-related musculoskeletal disorders due to prolonged static postures and asymmetrical movements. Despite the prevalence of these disorders, objective ergonomic assessments in orchestral settings are limited.

**Objective:**

The primary aim of this study (the Orchestral Posture Ergonomic Assessment [OPErA] project) is to quantify postural deviations in professional orchestral musicians, with and without their instruments, and to investigate their association with pain and pain leading to performance limitation. Secondary aims include exploring demographic, clinical, and occupational factors associated with these outcomes.

**Methods:**

This cross-sectional study will enroll 250 professional musicians from Italian orchestras, excluding pianists. Postural assessments will be conducted in 2 phases—without and with the instrument—using the Physical Analyzer Portable, a device for calibrated photo acquisition. Anatomical landmarks will be marked with electrocardiogram electrodes to measure inclination, rotation, and asymmetries in the frontal and sagittal planes. Pain and disability will be evaluated using validated questionnaires (Quick Disabilities of the Arm, Shoulder and Hand [QuickDASH]; Modified Oswestry Disability Index; and Neck Disability Index). Statistical analysis will include descriptive statistics, 2-tailed *t* tests, chi-square tests, and regression models to explore associations between posture and pain.

**Results:**

The protocol was approved in November 2022 and funded in 2025. Data collection was conducted from May 2023 to April 2026. By the time of manuscript submission (February 2026), 240 of the target 250 participants had been enrolled. Data analysis is ongoing, and the results are expected to be published in July 2026.

**Conclusions:**

This study will provide quantitative insights into postural deviations and their relationships with pain and pain leading to performance limitation. The findings are expected to identify instrument-specific associated factors and compensatory behaviors, supporting the development of targeted ergonomic interventions and preventive strategies for musicians’ health.

## Introduction

### Background and Rationale

Movement is essential for musicians, enabling them to express creativity and connect with their audience. The integration of body and instrument creates an impression of effortless harmony, free from tension and pain. However, this idealized image often obscures the reality of musculoskeletal and neurological disorders that can affect musicians, limit performance, and, in some cases, end careers prematurely. Musicians often ignore pain and symptoms that need attention and rest [1].

Bernardino Ramazzini first described occupational diseases in musicians in 1713. Zaza et al [2] introduced the term playing-related musculoskeletal disorders (PRMDs) to describe musculoskeletal symptoms, such as pain, weakness, numbness, or loss of coordination, that are caused or exacerbated by playing a musical instrument and are severe enough to impair a musician’s ability to perform at their usual technical level. In this definition, a condition qualifies as a PRMD only when it interferes with musical performance, distinguishing it from symptoms that may occur in everyday life but do not affect playing. Zaza et al [2] further emphasized that PRMDs can become chronic and disabling, affecting musicians not only physically but also emotionally and socially [3]. Reviews report high prevalence rates of musculoskeletal disorders among musicians, with rates ranging from 57% to 68% for general issues, 9% to 68% for PRMDs, and 62% to 93% for one-time PRMDs [1,4,5]. Studies, such as those by Fishbein et al [6], show that many musicians, including 76% of International Conference of Symphony and Opera Musicians members, experience medical issues that compromise their performance.

Identifying risk factors for PRMDs is crucial for prevention [7]. Common factors include gender, age, professional status, years of experience, type of instrument, repertoire, technique, long practice hours, poor physical condition, muscle fatigue, lack of preventive behaviors, and previous injuries. Psychological stress factors, such as anxiety, depression, and perfectionism, also correlate with musculoskeletal disorders [1,4,8]. The weight of the instrument and playing posture can influence injury prevalence.

Research confirms that prolonged forced body positions increase the likelihood of musculoskeletal overload. Few studies focus on the impact of playing classical instruments on posture [9]. Musicians spend about 1300 hours per year in ergonomically unfavorable positions. Instruments requiring different playing positions and techniques have varying prevalence rates of musculoskeletal disorders [10]. A study among conservatory students found high rates of postural alterations without the instrument (66.2%) and nonoptimal posture with the instrument (73.4%). Asymmetrical postures, such as those required by the violin, viola, and flute, are significant associated factors [11].

Musicians playing with arms above the scapulohumeral plane are more prone to PRMDs in the upper limbs [12]. Addressing these conditions requires understanding the factors and implementing appropriate measures. Reviews on ergonomic assessment in orchestra musicians indicate a lack of publications on this topic [13]. More information is available on questionnaires assessing symptoms, such as the “standardized Nordic Musculoskeletal Questionnaire” [14] and the Disabilities of the Arm, Shoulder, and Hand [15].

Compensatory behaviors can be a significant associated factor linked to musculoskeletal disorders among musicians. Understanding and addressing these behaviors is essential for effective prevention and management.

### Objectives

The study aims are to investigate the frequency and types of postural changes, both while musicians are playing their instruments and when they are not, and evaluate whether these postural changes are associated with pain and pain leading to performance limitation. The study will also explore additional associated factors with postural changes and pain based on the demographic, clinical, and musical activity information obtained through the questionnaire.

Finally, it will explore how these postural issues affect the professional lives of musicians.

## Methods

### Study Design

The study design chosen for this project is cross-sectional.

#### Study Setting

The setting will not be standardized: postural assessments will be performed in the various sites of the participating orchestras. Image acquisition was conducted in private changing rooms provided by the hosting institutions (eg, theaters), following an explicit request from the head of Smart Homes, Assistive Technologies, and Occupational Therapy unit. Only the researcher responsible for image collection was present during the procedure; the physician supervising participant enrollment could enter the room only if required. Images were stored on a secure institutional server with restricted access. Raw photographs, which included participants’ faces, can be accessed exclusively by the medical members of the research team and the therapist involved in enrollment. The data collected will be processed and stored by Fondazione Don Carlo Gnocchi for the time necessary to achieve the purposes of the specific study, in compliance with the principle of data minimization and with legal obligations. After this period, the data will be retained for 10 years following the conclusion of the study. The key linking patient identity and study ID will be kept by the principal investigator in a protected file stored outside the digital database for the duration of the study and will be deleted at its completion.

#### Eligibility Criteria

Inclusion criteria were being a professional musician in an Italian orchestra, being aged >18 years, belonging to either sex, and having signed the informed consent form. The only exclusion criterion was having the piano as the primary instrument, owing to the logistical challenges associated with its size and transportability, which precluded standardized evaluation.

#### Interventions and Outcomes

Demographic, medical history, and musical activity data will be collected using a specifically designed questionnaire. This questionnaire will also gather information on rehearsal frequency and playing duration during the previous week, as these variables represent more stable and comparable exposure indicators across participants. Conversely, information regarding rehearsal conditions and playing duration on the day of assessment will not be collected, as these factors exhibit substantial day-to-day variability, cannot be standardized across orchestra settings, and are unlikely to exert a reproducible influence on static postural parameters.

The questionnaire used in this study is not a validated instrument; it was developed based on the research team’s clinical experience. It was administered in Italian. Participants were first asked to report any history of performance-limiting pain throughout their entire professional career. Subsequently, targeted questions evaluated the presence of pain and PPL during the preceding week, allowing the distinction between lifetime occurrence and recent symptoms.

The impact of painful symptoms during last week on professional and nonprofessional activities will be assessed using the “QuickDASH” scale for the upper limb disability [16], the “Modified Oswestry Low Back Disability Index” for low back pain [17], and the “Neck Disability Index” questionnaire for neck pain and cervicodorsal symptoms [18].

Postural evaluation will consist of 2 phases: phase 1 without the instrument in a sitting position and phase 2 with the musical instrument in a sitting position. To improve the precision of the examination during data acquisition, participants will be asked to remain shirtless if male or wearing only a bra if female. Disposable electrocardiogram electrodes will be applied to anatomical landmarks. These electrodes are used exclusively as anatomical markers and not for recording electrical activity. They consist of circular adhesive pads with a base diameter of approximately 30 mm to 40 mm and a small, raised apex of a few millimeters, which facilitates precise landmark identification. The following anatomical landmarks were identified: spinous process C7 (C7), right shoulder acromion (RS), left shoulder acromion (LS), right scapula inferior angle (RIA), left scapula inferior angle (LIA), spinous process L3 (L3), intergluteal line (IG), glabella (GL), and sternal notch (ST).

Participants were seated on a standardized stool (height: 47 cm; leg separation: 26.5 cm), except for the double bass players who used a chair provided by the orchestra without a backrest due to the instrument’s size and ergonomic requirements. The stool, the chair, and the camera were placed in fixed positions, which were marked on a mat included in the kit, and the instrument was calibrated according to these distances.

For photos without the instrument, participants kept their arms relaxed alongside the body. For photos with the instrument, hand placement followed the standard playing position (a position for string instruments). In both phases, the Physical Analyzer Portable will be used—a noninvasive, portable device that allows calibrated photo acquisition on the frontal and sagittal planes and subsequent data processing through dedicated software. This device is not formally validated but it is aligned with the principles of clinical posture assessment presented in the study by Fortin et al [19]. The following measurements will be taken with and without the musical instrument.

As far as the frontal plane is concerned, the following parameters will be measured: trunk inclination on the frontal plane: angle between C7 and IG, head-neck inclination: angle between ST and GL, right shoulder height: distance between RS and the horizontal line passing through C7, left shoulder height: distance between LS and the horizontal line passing through C7, right shoulder width: distance between RS and the vertical line passing through C7, left shoulder width: distance between LS and the vertical line passing through C7, right scapula–rachis distance: distance between RIA and the vertical line passing through C7, and left scapula–rachis distance: distance between LIA and the vertical line passing through C7.

As far as the sagittal plane is concerned, the following parameters will be measured: cervical arrow: distance between the vertical tangent to the apex of the dorsal kyphosis and C7, lumbar arrow: distance between the vertical tangent to the apex of the dorsal kyphosis and L3, right shoulder distance: distance between RS and the vertical line passing through C7, and left shoulder distance: distance between LS and the vertical line passing through C7. We will numerically quantify trunk rotation and right-left shoulder asymmetry in both conditions (with and without the instrument). Furthermore, we will compute all between-condition differences to assess postural changes attributable to instrument use. All distances are measured in millimeters, and all angles are measured in degrees.

Musical instruments will be classified into 2 main categories: symmetric and asymmetric [11], and the postural measures will be analyzed based on this categorization. Further exploratory analyses may also be conducted on specific instrument families.

#### Timeline

The project phases were implemented according to an indicative timeline spanning November 2022 to December 2024. The initial phase involved defining the clinical framework of the OPErA (Orchestral Posture Ergonomic Assessment) project and preparing the documentation for submission to the ethics committee. This was followed by orchestra recruitment, implementation of the study protocol, data collection and analysis, and the preparation of related reports.

#### Sample Size

A total of 250 participants will be enrolled. Regarding the primary objective of the study, which is to investigate the prevalence and types of postural alterations, it is estimated that—assuming a prevalence of 50%—a sample of 250 participants will allow for an estimation of the prevalence with a significance level of α=5% and a precision (semiwidth of the CI) of 6%, using the binomial model with normal approximation for the calculation of the CI.

Participant recruitment will be conducted following ethics committee approval and registration of the study on ClinicalTrials.gov, with an anticipated recruitment period of 30 months.

Participation in the study will be voluntary and will require written informed consent. All musical instruments will be eligible for inclusion and will be classified as either symmetrical or asymmetrical for analysis purposes.

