### Association With Pain and Disability (Secondary Aims)

To examine factors associated with the outcomes of pain and performance-limiting pain, logistic regression models will be used. The dependent variables will be the presence of pain during the preceding week and the presence of performance-limiting pain during the preceding week, both operationalized as binary outcomes. Independent variables will include demographic characteristics (eg, age and gender), occupational factors (eg, instrument type [classified as symmetric or asymmetric], years of professional experience, and practice hours), and postural delta values, which represent instrument-induced postural changes as described above.

To investigate factors associated with the severity of disability, as measured by the QuickDASH, Oswestry Disability Index, and Neck Disability Index scores, linear regression models (or quantile regression models, if model assumptions are violated) will be used, incorporating the same set of independent variables.

Variables achieving a *P* value of <.10 in univariate analyses will be entered into multivariable models to identify independent predictors. Results will be reported as odds ratios or regression coefficients with their corresponding 95% CIs. A *P* value of <.05 will be considered indicative of statistical significance in all final models.

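### The 6% precision assumes independent musicians although recruitment runs through orchestras, and the pain and disability regressions name no orchestra term; intervals will be too narrow if outcomes correlate within orchestras

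*Protocol article*

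**What the plan says.** All places are in the protocol article.

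- **Sample Size.** "A total of 250 participants will be enrolled". The precision is worked out "assuming a prevalence of 50" percent, with "a significance level of α=5% and a precision (semiwidth of the CI) of 6" percent, "using the binomial model with normal approximation for the calculation of the CI". No design effect is applied.
- **Timeline.** After the preparatory phase: "This was followed by orchestra recruitment, implementation of the study protocol, data collection and analysis". Orchestras are therefore the route by which musicians enter the study.
- **Study Setting.** "The setting will not be standardized: postural assessments will be performed in the various sites of the participating orchestras". The Recruitment section repeats that assessments take place where the orchestras are based.
- **Interventions and Outcomes.** Pain, performance-limiting pain, rehearsal frequency and playing duration all refer to the preceding week. On the measurement set-up: "The stool, the chair, and the camera were placed in fixed positions, which were marked on a mat included in the kit".
- **Association With Pain and Disability (Secondary Aims).** For the two binary pain outcomes, "logistic regression models will be used". Linear or quantile regression serves the disability scores. The covariates listed are demographic, occupational and postural. Orchestra is not among them, and no random effect or robust standard error is mentioned.
- **Anticipated Findings.** Variability between environments is accepted as a limitation, with no analytic handling.

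**The concern.** Musicians in one orchestra are not obviously independent draws. In any given week they can be expected to share a programme and a rehearsal load, and both pain outcomes are measured over that week. Any shared influence of this kind makes colleagues resemble each other, so 250 musicians carry less information than 250 independent ones.

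Two parts of the plan are exposed:

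- **Prevalence intervals.** The stated precision concerns postural alterations. The Discussion also expects to estimate the prevalence of pain and performance-limiting pain, where within-orchestra correlation is more plausible.
- **Pain and disability regressions.** Ordinary standard errors are too small mainly for covariates that vary between orchestras, such as playing load. Covariates that vary within an orchestra, such as instrument type, are less affected. Orchestra can also act as a confounder if it drives both exposure and outcome.

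At stake are the width of the reported intervals, the P values of the final models, and the accuracy of the one precision figure on which the sample size rests.

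**Working it through.** **Inputs from the article:** n = 250, prevalence p = 0.50, two-sided α = 5% (z = 1.96), stated half-width 6%.

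**Inputs that are assumptions:** within-orchestra ICC and musicians per orchestra m. The article gives neither, nor the number of orchestras. ICC from 0 to 0.05 and m of 10, 25 and 50 are used here; with 250 musicians these sizes correspond to 25, 10 and 5 orchestras of equal size.

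**Step 1: the plan's own figure.** Half-width = z·√(p(1−p)/n) = 1.96·√(0.25/250) = 6.20%. This matches the stated 6% at whole-percent rounding.

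**Step 2: allow for clustering.** Design effect DE = 1 + (m−1)·ICC; half-width = 6.20%·√DE; effective n = 250/DE.

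| ICC | m = 10 | m = 25 | m = 50 |
|---|---|---|---|
| 0 | 6.20% | 6.20% | 6.20% |
| 0.01 | 6.47% | 6.90% | 7.57% |
| 0.02 | 6.73% | 7.54% | 8.72% |
| 0.05 | 7.46% | 9.19% | 11.51% |

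Three cells in full:

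- ICC 0.01, m = 10: DE = 1 + 9·0.01 = 1.09; effective n = 229.
- ICC 0.02, m = 25: DE = 1 + 24·0.02 = 1.48; effective n = 169.
- ICC 0.05, m = 25: DE = 1 + 24·0.05 = 2.20; effective n = 114.

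**Step 3: coverage of the unadjusted 95% interval.** Coverage = 2Φ(1.96/√DE) − 1. For the same three cells this is 94.0%, 89.3% and 81.4%.

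**Step 4: how much correlation the stated figure tolerates.** To stay below 6.5%, and so still round to 6%, DE must be below (6.5/6.198)² = 1.10. That means an ICC below 0.10/9 ≈ 0.011 at m = 10, 0.10/24 ≈ 0.004 at m = 25, or 0.10/49 ≈ 0.002 at m = 50.

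**Step 5: the paired comparison.** The main comparison uses each musician's value with the instrument minus the value without it. If an orchestra or site adds the same amount s to both, the delta is (x₁ + s) − (x₀ + s) = x₁ − x₀, and s disappears. Only variation between orchestras in the deltas themselves would remain.

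**The case against.** The strongest reply is that the loss is conditional. A reader might infer that the 6% is not delivered and that every interval and model in the study is too narrow. The documents do not support that. They give no ICC and no cluster size. At ICC 0 nothing is lost, and at ICC 0.01 with ten musicians per orchestra the half-width still rounds to 6%. The main comparison is within-subject, so a common site effect cancels.

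Further points for the plan:

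- **Set-up.** The lack of standardisation concerns the venues. Stool dimensions, positions on the mat and camera calibration are fixed, and only double bass players use an orchestra chair. This answers much of the worry about posture measurements sharing a site effect. Each orchestra also mixes instruments, so much of the postural variation should lie within orchestras.
- **Playing load.** Rehearsal frequency and playing duration are recorded per person, and practice hours are a candidate covariate, so a shared workload is partly addressed.
- **Choice of 50%.** This is the least favourable prevalence. At the 66.2% and 73.4% that the Introduction cites for conservatory students, the independent half-widths are 5.9% and 5.5%, which leaves a little slack.
- **Unseen plan.** A statistical analysis plan may exist and could specify mixed models or robust standard errors.

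These points narrow the concern without removing it. An unseen plan cannot change the independence assumption behind the published precision figure, and the regression section does set out models and covariate groups without orchestra. The slack from a higher prevalence keeps the half-width at 6.0% only up to a design effect of about 1.05 (at 66.2%) or 1.20 (at 73.4%).

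A reader might also object that an exact 6.0% needs 267 participants. That is rounding of 6.2%, not an error in the plan.

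**Conclusion.** The concern holds in conditional form. The stated precision rests on independence, the recruitment route gives reason to doubt it, and the secondary-aim regressions as described do not allow for orchestra.

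Under the assumed values the loss runs from nil to substantial. With up to 25 musicians per orchestra and an ICC up to 0.05, the half-width lies between 6.2% and 9.2%; larger orchestra samples would make it worse. The formula takes orchestras to be of equal size. No single figure in that range can be presented as the study's true precision.

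The exposed parts are the prevalence intervals and the past-week pain and disability models. The paired postural comparison is largely protected. This should be changed before the analysis is completed, but it does not undermine the design.

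**What to change.** 1. **Keep the orchestra identifier.** Confirm that orchestra is a field in the pseudonymised database. The data examples in Ethical Considerations do not name it, and the identity key is to be deleted at study end. If the field is absent, add it before the key is deleted.
2. **Report the clustering.** Give the number of orchestras and the distribution of musicians per orchestra.
3. **Analyse accordingly.** Compute the prevalence intervals and fit the pain and disability models with cluster-robust or GEE standard errors, using a small-sample correction if orchestras are few, or with a random intercept for orchestra.
4. **Treat confounding separately.** Robust standard errors and GEE do not remove confounding by orchestra, and a random intercept does so only in part. If it is a concern, add a sensitivity analysis with orchestra fixed effects.
5. **Qualify the precision statement.** Say in Sample Size that 6% holds under independence, and give a design-effect range with the ICCs and cluster sizes labelled as assumptions.

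No new participants are needed, and SPSS has mixed-model and GEE procedures. The cost is wider intervals where correlation is present and a less favourable stated precision.
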